##### Process evaluation

We will conduct a process evaluation to assess other parts of the RE-AIM framework. In short, the RE-AIM framework has been developed to evaluate public health interventions assessing five dimensions (reach, efficacy, adoption, implementation and maintenance) at multiple levels (eg, individual or organisation).^18^
*Reach* will be assessed by measuring the participation rates and representativeness of patients who participate in this study. In case a patient refuses or discontinues to participate in this study, the patient’s age, gender and BP-lowering drugs the patient uses will be recorded by research assistants. This information is used to calculate the participation rate and assess differences between responders and non-responders. To determine representativeness, the patients’ demographics will be compared with census demographics in Bandung City, Indonesia. *Adoption* will be evaluated by assessing the proportion and representativeness of CHCs who participate in this study, and exploring pharmacists’ and patients’ satisfaction with and willingness to use various parts of the intervention. *Implementation* will be evaluated by determining whether the intervention was delivered as intended and exploring pharmacists’ and patients’ suggestions for future implementation. *Maintenance* will be assessed by determining whether the intervention can be maintained and the willingness of pharmacists and payers to continue the intervention as part of routine clinical practice. We will use focus group discussions at a 1-month (T1) follow-up and an evaluation survey (based on a previously used survey)^28^ at a 3-month follow-up (T2) to explore pharmacists’ and patients’ adoption, implementation and willingness to maintain the intervention, respectively.

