### Sample size calculation

The sample size calculation is based on the formula for cluster randomised trials, powered on the primary outcome.^29^ We want to be able to detect a difference between the intervention and control group in the change in adherence score of at least 2.5 points with an expected SD of 3.8 points and assuming an intracluster correlation coefficient within CHCs of 0.014, as calculated based on the previous work from our group (manuscript in preparation). A sample size of 41 non-adherent patients in each study arm (intervention and control group) would allow for 80% power to detect this difference using a two-sided test at the 5% level of significance. Assuming non-adherence rates of 50%^30^ and a dropout rate of 20%, we will recruit at least 100 patients in each group, giving a total of 200 patients from 10 CHCs (20 per CHC) that need to complete the MARS screening. Recruiting at least 20 patients per CHC is feasible as the average number of diabetes patients with hypertension visiting a CHC is around 30 patients per month.

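### The recruitment target counts patients screened, gives 40 completers per arm against the stated 41, and leaves no reserve for refusals

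*Protocol article*

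**What the plan says.** All the figures are in the Protocol article, Sample size calculation.

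- The design looks for a "change in adherence score of at least 2.5 points with an expected SD of 3.8 points", "assuming an intracluster correlation coefficient within CHCs of 0.014".
- The requirement is given as "A sample size of 41 non-adherent patients in each study arm (intervention and control group"), which "would allow for 80% power to detect this difference using a two-sided test at the 5% level of significance".
- The step to a recruitment number begins "Assuming non-adherence rates of 50"% and adds 20% dropout. It ends: "we will recruit at least 100 patients in each group, giving a total of 200 patients from 10 CHCs (20 per CHC"). The sentence closes by describing these 200 as the patients who have to complete the MARS screen.
- Feasibility is argued at 20 per CHC, from a flow of about 30 diabetes patients with hypertension per CHC per month.

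Two other sections bear on the count. Under Participants, the pharmacist screens for eligibility, and an eligible patient is then approached for consent. Under Process evaluation, the text that begins "In case a patient refuses or discontinues to participate in this study" provides for recording the characteristics of such patients and for calculating a participation rate.

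**The concern.** Three quantities need to be kept apart: patients screened, patients enrolled (MARS <20 and consenting), and patients with a 3-month outcome. The power statement concerns the third. The recruitment target is set in the first, although the verb used is the one normally kept for enrolment. No enrolled number is given per arm or per CHC.

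This has two consequences. The conversion from 41 back to screened patients can be checked, and it does not come out at 100. Also, a target counted in screened patients can be met whatever number prove non-adherent and agree to take part, so reaching it does not secure the 41. At stake is whether the stated size, and the power resting on it, is what the recruitment plan would deliver.

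**Working it through.** **Inputs (Sample size calculation, unless noted).** Difference 2.5; SD 3.8; ICC 0.014; 80% power, two-sided 5%; 41 per arm; non-adherence 50%; dropout 20%; 100 screened per arm, 20 per CHC. Five CHCs per arm (Intervention; Control group).

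**1. The plan's 41.** Unadjusted size per arm: 2 × [3.8 × (1.960 + 0.842) / 2.5]² = 36.3, rounded up to 37. With 8 patients per CHC (about 41/5) the design effect is 1 + 7 × 0.014 = 1.098, and 37 × 1.098 = 40.6, so 41. With 10 per CHC it is 1.126, and 36.27 × 1.126 = 40.8, also 41. The stated 41 is reproduced.

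**2. From 100 screened to completers.** 100 × 0.50 = 50 non-adherent; 50 × 0.80 = 40 completers per arm, or 8 per CHC. This is one below 41.

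**3. From 41 back to screened.**
- Enrolled: 41 / 0.80 = 51.25, so 52 per arm, or 52/5 = 10.4 per CHC.
- Screened: 41 / (0.80 × 0.50) = 102.5, so 103 per arm. Rounding at the enrolment step first gives 52 / 0.50 = 104.
- In equal whole numbers per CHC: 21 per CHC, 105 per arm, 210 in total, which covers both roundings.

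Multiplying by 1.20 in place of dividing by 0.80 gives 41 × 1.20 / 0.50 = 98.4, close to 100. That may be the source of the figure, but the document does not say.

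**4. Power at n completers per arm.** Design effect D = 1 + (n/5 − 1) × 0.014; SE = 3.8 × √(2D/n); power = Φ(2.5/SE − 1.960).
- n = 41: D = 1.101, SE = 0.881, power 81.0%.
- n = 40: D = 1.098, SE = 0.890, power 80.2%.

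**5. Refusals.** The document gives no rate, so the rates here are assumptions. With refusal r among eligible patients, expected completers are 40 × (1 − r), and the screened number needed is 41 / [0.40 × (1 − r)].

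| Assumed refusal | Completers per arm from 100 screened | Power | Screened per arm for 41 completers | Per CHC |
|---|---|---|---|---|
| 0% | 40 | 80.2% | 103 | 21 |
| 5% | 38 | 78.3% | 108 | 22 |
| 10% | 36 | 76.3% | 114 | 23 |
| 20% | 32 | 71.8% | 129 | 26 |

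**6. Chance of reaching the count.** Treating screened patients as independent, each with a 0.4 chance of becoming a completer, P(at least 41 of 100) = 46% and P(at least 40) = 54%. With 52 enrolled and 80% retention, P(at least 41) = 66% in one arm and 0.66² ≈ 43% in both.

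**The case against.** - **The gap is a rounding difference.** This stands. Forty against 41 leaves power at about 80%.
- **A reader might infer that the trial will more likely miss its size than meet it.** The 46% invites this, but the cut-off lies one above the expected 40, and moving it to 40 gives 54%. Any target set at expected need behaves this way: 52 enrolled would itself reach 41 in both arms only about 43% of the time. The argument carries no weight.
- **A reader might infer that CHCs stop at 20.** Nothing instructs them to. Both the per-arm and the per-CHC numbers are worded as minimums, and the sentence discloses that it counts screening. The unit is loosely named, not concealed. Even so, a minimum in screened patients gives no enrolled number to continue towards.
- **The refusal losses are assumed.** They are. Recording refusals to measure reach does not show that they will be common. The eligibility list also names signed consent before the MARS criterion; if all 100 had already consented, the refusal rows would not apply. The recruitment narrative, however, places the approach for consent after eligibility is established, and no consent allowance is made on either reading.
- **This is a condensed article.** Screening logs and continuation rules may well be in the full protocol, and their absence is not held against the plan. The point rests on the conversion and the unit that the article itself states.

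**Conclusion.** The point holds in limited form. On the plan's own rates the stated screening target gives 40 completers per arm, not 41; the figure should be 103 screened per arm (21 per CHC, 210 in total), equivalent to 52 enrolled. The target is set in screened patients and has no reserve.

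No loss of power is shown by the arithmetic alone. A loss arises only if eligible patients refuse: about 2 percentage points from 80.2% at 5% refusal, 4 at 10% and 8 at 20%. These figures depend on the assumed rates, on consent following the MARS screen, and on 50% non-adherence and 20% dropout holding. They use a normal approximation, which makes no allowance for there being only five CHCs per arm.

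**What to change.** 1. Correct the screening figure to at least 103 per arm, in practice 21 per CHC and 210 in total, before any allowance for refusal.
2. State the recruitment target as at least 52 consenting patients with MARS <20 per arm (10–11 per CHC), alongside the 41 completers it is meant to give.
3. Keep the screened number as a workload estimate with an explicit consent assumption; 10% refusal, for example, would mean about 23 per CHC.
4. Continue screening to the enrolled target within the planned recruitment window. If the target cannot be reached in that time, restate the expected completers and the power.

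The cost is a change of wording and some extra screening where yield is low. The stated flow of about 30 patients per CHC per month suggests this is attainable, since even 20% assumed refusal needs 26 per CHC. The room is not unlimited: August to December with a 3-month follow-up leaves roughly two months to recruit (5 − 3), and the article does not say how many second-month visitors would be new patients. Design and analysis are unchanged.

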### Planned statistical analysis

Data analysis will be performed based on the intention-to-treat principle. Descriptive statistics will be used to summarise the baseline characteristics. To control for the effects of cluster randomisation, group changes will be compared (individual CHCs will be treated as a random effect) using multivariate mixed linear and non-linear regression for normally and non-normally distributed data, respectively. Point estimates estimated from cluster-adjusted models will be reported with 95% confidence intervals . We will conduct subgroup analysis using data stratification on diabetes complications and the number of concomitant medications to assess the effect of the intervention. All tests will be two-tailed and p*<*0.05 will be considered statistically significant. All statistical analyses will be carried out using SPSS software (V.25).

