### Participants

A total of 10 CHCs will be purposively selected based on a sufficient number of patients with type 2 diabetes with hypertension. The principal investigator (PI) will introduce and explain the study to the pharmacists and physicians in the CHCs. In each CHC, one pharmacist will be included. In Indonesia, one of the pharmacist’s responsibilities during routine clinical practice is to counsel patients with chronic diseases on their medication use, often performed in a counselling room that is separated from the drug counter.^19^ Screening for patients’ eligibility will be conducted by the pharmacist during regular outpatient visits. Once a patient is deemed eligible, the pharmacist will inform the PI or research assistant to approach the patient and briefly explain the study, and ask to sign informed consent (online supplementary appendix B). Patients will be eligible if they meet the following inclusion criteria: (i) at least 18 years old, (ii) diagnosed with type 2 diabetes for at least 1 year based on patient’s medical record, (iii) using at least one antihypertensive drug in the last 3 months, (iv) have signed informed consent and (v) have suboptimal medication adherence to antihypertensive drugs according to the Medication Adherence Report Scale (MARS score <20; MARS scores range from 5 to 25). Of note, our previous work in four regions in Indonesia (Bandung City, Yogyakarta City, Makassar City and Samarinda City) showed that half of the patients were non-adherent, with a MARS score <20. Patients with severe mental or physical constraints, pregnancy or in the lactation period, illiterate in the Indonesian language, enrolment in another intervention study and those not responsible for taking their own medication will be excluded.

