### Outcomes

#### Primary outcome

The primary outcome is the difference between the intervention and the control group in the change in the MARS score from baseline (T0) to a 3-month follow-up (T2). The Indonesian version of the MARS showed to be valid (correlation value of each question to the total score >0.396) and reliable (Cronbach α coefficient of 0.803).^25^ Patients will indicate how often each statement applied to them in the last 3 months on a 5-point Likert scale ranging from always (score 1) to never (score 5). Items are summed to obtain a total score ranging from 5 to 25 (Horne R. The Medication Adherence Report Scale (MARS): a new measurement tool for eliciting patients’ reports of non-adherence).

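### The protocol lets the observed distribution of the data decide the primary model for MARS change, and so possibly the scale of the primary result

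*Protocol article*

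**What the plan says.** Under Primary outcome, the protocol article fixes the outcome as the between-arm difference in change in MARS score from baseline (T0) to 3 months (T2). On the scale it says: "Items are summed to obtain a total score ranging from 5 to 25". Under Participants, entry requires a low score: "MARS score <20; MARS scores range from 5 to 25".

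Under Sample size calculation, the target is a "difference between the intervention and control group in the change in adherence score of at least 2.5 points". The other inputs are an assumed SD of 3.8, an intracluster correlation of 0.014, 80% power and a two-sided 5% test. This gives 41 non-adherent patients per arm.

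Under Planned statistical analysis, group changes are compared with the health centre as a random effect, "using multivariate mixed linear and non-linear regression for normally and non-normally distributed data, respectively". The section adds: "Point estimates estimated from cluster-adjusted models will be reported with 95% confidence intervals". Nothing there sets the primary outcome apart from the others.

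Under Randomisation and blinding, the principal investigator is not blinded. Under Data management, the same person enters the data.

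**The concern.** The outcome variable is fixed in advance, but the model used to estimate the effect is not. The stated trigger is whether the data are normally distributed, which is known only once they have been collected.

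This matters for two reasons. First, a linear mixed model returns a mean difference in MARS points, which is the quantity the protocol defines and powers. A non-linear mixed model may return another measure, such as an odds ratio or a ratio. The report is to give the estimates of the cluster-adjusted models, so on that branch the headline result might not be comparable with the 2.5-point target. Second, a primary analysis whose form depends on the outcome data is harder to defend when the principal investigator knows the allocation and handles the data.

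This is not a complaint about detail that a condensed article leaves to an analysis plan. A normality criterion and a link function could well be given elsewhere. The difficulty is the rule that the article itself states: supplying a criterion would make the switch reproducible, but the data would still choose the primary model.

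**Working it through.** **1. What the sample size rests on.**

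Inputs from Sample size calculation: difference d = 2.5, SD s = 3.8, intracluster correlation 0.014, two-sided 5%, power 80%. The normal quantiles sum to 1.960 + 0.842 = 2.802.

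- Unadjusted n per arm = 2 × (s × 2.802 / d)² = 2 × (3.8 × 2.802 / 2.5)² = 36.27.
- Cluster size m = 10 is my inference: 20 screened per centre × 50% non-adherent.
- Design effect = 1 + (10 − 1) × 0.014 = 1.126.
- n per arm = 36.27 × 1.126 = 40.84, rounded up to **41**. This is the protocol's figure.
- Power with 41 per arm at m = 10 is 80.2%.

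Other cluster sizes do not give 41 exactly: m = 8 gives 39.82 (40) and m = 20 gives 45.92 (46).

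Every input is in MARS points, so the calculation powers a mean difference. No odds ratio, ratio or other measure is given on which a non-linear model could be powered.

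**2. Which outcomes the rule acts on.**

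| Outcome compared for change | Type |
|---|---|
| MARS total | integer sum, 5 to 25 |
| Systolic and diastolic pressure | continuous |
| BMQ necessity, concerns, differential | numeric scores |
| BMQ side-effect item | single 5-point ordinal item |

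Only the last is not a numeric score. The rule therefore acts mainly on numeric outcomes, including the primary one.

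**3. Could the trigger plausibly be met for MARS?**

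The documents give no MARS distribution, so this is an illustration under assumptions:

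- 41 per arm in 10 centres, intracluster correlation 0.014, treatment effect 2.5 points, mean gain in controls 1.5 points before capping.
- Scores rounded to integers; baseline restricted to below 20; follow-up held between 5 and 25.
- Underlying baseline mean 14, 16, 18 or 20 with SD 2 or 3 before truncation; SD of the error in change 3.8 or 4.2.
- 1,000 simulated trials per setting; Shapiro-Wilk test at 5%.

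| Quantity checked | Share of trials in which normality is rejected, range over settings |
|---|---|
| Change score | 12% to 94% |
| T2 score | 18% to 100% |
| Residuals within arm | 7% to 72% |

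Rejection is least frequent when baseline scores lie well below the cut-off and most frequent when they crowd against it. The branch taken thus depends on the data that arise and on the quantity examined. The article does not fix either.

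**The case against.** **The rule may only match model to outcome type.** On this reading, the linear model is for scores and the non-linear one for categorical outcomes. The ordinal BMQ item gives this some footing. But the trigger in the text is normality, not outcome type, and MARS is not assigned to either branch. If the benign reading is what was meant, the proposed sentence simply says so.

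**The effect measure is already fixed.** The primary outcome and the sample size are both stated as a difference in score. That is right, and a reader should not infer that the points estimate would necessarily be lost. A model for non-normal data with an identity link would still report points, and descriptive mean changes would remain available. What stands is that the analysis section does not carry the points scale over into the model, so its loss is possible.

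**Type I error.** A reader might infer two chances to reject, and so up to 1 − 0.95² = 9.75%. The documents do not support this. The rule assigns one model; it does not run two and keep the smaller p-value. Nor is 9.75% a true ceiling, since under arbitrary dependence the limit for two tests is 10%. One null simulation took a cluster-level t-test of log(26 − T2) as an assumed alternative and switched on the residuals. It rejected in 4.9% to 5.5% of trials over three baseline settings; taking the smaller p-value at will rejected in 7.5% to 8.0%. These figures depend on the assumed alternative. The protocol names none, so no inflation can be attributed to it.

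**Unblinding.** The article does not say that anyone would choose the model knowing its result. Unblinding makes a data-dependent choice harder to defend; it is not evidence of a biased one.

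**Robustness.** If a mean difference at about 40 per arm tolerates moderate skew, a sensible alternative may often agree with it. That limits the practical damage, but it is also a reason why the switch is not needed.

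**Conclusion.** The point holds in a limited form. Followed as written, the normality rule lets the observed distribution decide the primary model for MARS change. The non-linear branch may then report a measure other than the difference in points that the protocol defines and on which its 41 per arm depends.

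The size of the problem is a possible mismatch of scale and a primary analysis that is not fixed in advance. It is not a calculable error rate. The chance of a switch also cannot be stated for this trial: the simulated ranges rest on assumed baseline distributions and an assumed normality test, and show only that a switch is plausible. The mismatch with the power basis does not depend on the simulation. It follows from setting the outcome, sample size and analysis sections side by side.

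The point concerns the primary outcome. It does not require a change for blood pressure or BMQ, to which the sample size argument does not apply.

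**What to change.** In Planned statistical analysis, state that the primary analysis of change in MARS from T0 to T2 is the linear mixed model with health centre as a random effect. It reports the mean difference in points with its 95% confidence interval whatever the observed distribution. Any non-linear or other model for MARS becomes a sensitivity analysis.

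The cost is one sentence. No patients are added, and the stated basis of 41 per arm is kept. The downside is that, with strong skew or a marked ceiling at 25, the linear model may be somewhat less efficient than a model suited to that shape. The sensitivity analysis would show this.

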Non-adherence may be more efficiently improved if only patients who need it are targeted and interventions are tailored to patients’ individual adherence barriers.^12 13^ Previous studies further suggested that effective interventions to improve adherence were led by a pharmacist, delivered face-to-face, administered directly to patients and behaviourally targeted compared with cognitively targeted interventions.^14^ In Southeast Asia, however, pharmacy services can be hampered by inadequate training of pharmacy staff.^15^ Furthermore, adherence interventions may not be sustained over time due to a lack of resources to maintain them. Thus, to improve adherence to antihypertensive drugs in patients with type 2 diabetes, a low-cost, targeted and tailored pharmacist-led intervention that can be integrated into the community pharmacy workflow is required.

The primary objective of this study is to assess the effect of a targeted and tailored pharmacist-led intervention on medication adherence to antihypertensive drugs among patients with type 2 diabetes. The secondary objectives are (a) to assess the effect of the intervention on blood pressure level and medication beliefs, (b) to evaluate the implementation of the intervention from a pharmacist and patient perspective and (c) to assess the effects of the intervention across different subgroups of patients.

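### Stratified analysis is the only method stated for the subgroup objective; it cannot show whether the effect differs between subgroups and could invite false contrasts

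*Protocol article*

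**What the plan says.** The last paragraph of the Introduction in the protocol article gives secondary objective (c) as "to assess the effects of the intervention across different subgroups of patients". The section Planned statistical analysis gives the method: "We will conduct subgroup analysis using data stratification on diabetes complications and the number of concomitant medications to assess the effect of the intervention". The next sentence says "All tests will be two-tailed" and sets significance at p<0.05 for every test.

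The same section plans mixed models with CHC as a random effect, and says that point estimates from the cluster-adjusted models will carry 95% confidence intervals. The article states no arm-by-subgroup interaction or other comparison between strata, and gives no number of strata, cut-off or expected subgroup size.

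The section Sample size calculation covers only the overall comparison.

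**The concern.** An analysis run separately in each stratum asks whether the effect there differs from zero. It does not ask whether the effect in one stratum differs from the effect in the other. If a reader of the results wants to know for whom the intervention works, the only tool on offer is a set of within-stratum results with a p<0.05 threshold beside each.

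The trial is sized for about 80% power overall, so each stratum has much less. One stratum can easily fall below the threshold and the other above it by chance, and this can look like effect modification. The intervention is targeted and tailored, and the article says that the findings are to guide scaling up. A spurious finding that it works with complications but not without them could misdirect that step.

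**Working it through.** **Inputs.** From Sample size calculation: "change in adherence score of at least 2.5 points"; "with an expected SD of 3.8 points"; "assuming an intracluster correlation coefficient within CHCs of 0.014"; "A sample size of 41 non-adherent patients in each study arm"; "80% power to detect this difference using a two-sided test at the 5% level of significance". From Intervention and Control group: five CHCs per arm.

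**The plan's own figure.** Unadjusted n per arm = 2 × (3.8 × (1.960 + 0.842) / 2.5)² = 36.3. With 10 patients per CHC the design effect is 1 + 9 × 0.014 = 1.126, and 36.27 × 1.126 = 40.8, so 41. The stated 41 per arm reproduces.

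**Assumptions, because the article does not give them.** Each factor has two strata, with splits from 50:50 to 80:20. The true effect is 2.5 points in both strata, and the two strata are treated as independent.

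**Power within a stratum.** With n patients per arm in the stratum:
- SE = 3.8 × √[(2/n) × (1 + (n/5 − 1) × 0.014)]
- power = Φ(2.5/SE − 1.96)

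For a 50:50 split, n = 20.5 (about 4 per CHC). The design effect is 1 + 3.1 × 0.014 = 1.043, SE = 1.21, and power = Φ(0.10) = 54%.

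**Chance that exactly one stratum is significant.** If the two powers are a and b, this is a(1 − b) + b(1 − a).

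| Split (41 per arm) | Power, smaller / larger stratum | Exactly one significant, normal | Same, t with 8 df |
|---|---|---|---|
| 50:50 | 54% / 54% | 50% | 49% |
| 60:40 | 46% / 61% | 51% | 50% |
| 70:30 | 37% / 68% | 55% | 53% |
| 80:20 | 26% / 73% | 61% | 57% |

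The t columns use 8 df (10 CHCs less 2). At 50:50 this lowers stratum power from 54% to 44% but hardly changes the chance of a discordant pair. Both strata come from the same CHCs, so their estimates are slightly correlated: covariance 2 × 0.014 × 3.8² / 5 = 0.081, and 0.081 / 1.21² ≈ 0.055. In the normal calculation, allowing for this lowers the figures by only 1 to 2 percentage points.

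**No effect at all.** The chance of at least one significant stratum in a two-level factor is 1 − 0.95² = 9.75%, about 10%. Over both factors it would be 1 − 0.95⁴ = 18.5% if the four tests were independent. They are not, because both factors divide the same patients, so about 19% marks the upper end of the range.

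**Interaction test instead.** When the effects are equal, it declares a difference in 5% of trials per factor. A shared CHC effect largely cancels from a difference between strata, so SE ≈ 3.8 × √(2/n₁ + 2/n₂), where n₁ and n₂ are the per-arm stratum sizes.
- 50:50: SE = 3.8 × √(4/20.5) = 1.68. Power for a 2.5-point difference between strata is Φ(2.5/1.68 − 1.96) = 32%. The difference detectable with 80% power is 2.80 × 1.68 = 4.7 points.
- 80:20: SE = 3.8 × √(2/8.2 + 2/32.8) = 2.10. Power is 22%, and the detectable difference is 5.9 points.

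**The case against.** The strongest reply is that the article can be read literally. Objective (c) speaks of effects across subgroups and does not say that they differ. Stratified estimates answer a question about the effect within each subgroup, and the planned 95% confidence intervals are a sound way to report them. Stratification does not exclude an interaction term, and an analysis plan that is not shown could add one, along with the medication cut-off and an exploratory label.

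Much of this stands. A reader might infer that the plan commits the trial to comparing significance between strata, or that false subgroup claims would follow from it. The article says neither. The missing cut-off is the kind of detail that an analysis plan can settle, and it is not part of this point. Whether to adjust for baseline MARS, or to enter the medication count as a linear term, is a separate choice.

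What the reply does not remove is that the article names a method. It is the only one given for an objective that spans subgroups, and it comes with a p<0.05 rule for every test. Looking across subgroups naturally leads to comparing them, and the stated method gives no valid way to do so.

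**Conclusion.** The point holds as a weakness in a stated method. Stratified analysis can describe the effect in each subgroup but cannot support a statement that the effect differs. If the true effect were the planned 2.5 points in everyone, a result significant in only one of two strata would occur in about 49–61% of trials per factor, against 5% for an interaction test. This rests on two strata per factor, the assumed splits, the protocol's SD and ICC, and about 41 evaluable patients per arm. It becomes a false conclusion only if someone reads the discordant pattern as a contrast, so the plan could invite such claims and does not itself make them. The point concerns secondary objective (c) only. The primary comparison and the sample size are unaffected.

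**What to change.** In Planned statistical analysis, amend the subgroup sentence as follows:
- Add an arm-by-subgroup interaction term to the planned mixed model, fitted to the full sample with CHC as a random effect, in one model per factor.
- Report the interaction estimate with its 95% confidence interval as the subgroup result.
- Show stratum-specific estimates with confidence intervals for description only, with no claims of significance within strata.
- Label all subgroup results exploratory.

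This changes wording and a model term only; it needs no further patients or data. The price is candour about precision. Power for a 2.5-point difference between strata is about 22–32%, and the difference detectable with 80% power is about 4.7 points even at a 50:50 split. The text should say so, and should add that a non-significant interaction does not show that the effect is the same in all subgroups.
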